#### Tertiary Outcome Measures

Life Space Assessment (LSA) is a 5-item scale that will be used to measure the size of the spatial area that an individual moves through in his or her daily life, as well as the frequency of his or her mobility within a certain timeframe [62]. Life space level (where participants travel) is measured dichotomously (yes/no), frequency is measured on a Likert Scale (1 to 4) from less than once/week to daily, and independence is measured in terms of the need for aids or equipment or assistance from another person. The total score for each item is the product of the life space level, frequency, and independence. All items are summed for a final score. Evidence for validity and test-retest reliability (*r*=.86) has been reported for older adults [63].

Modus Health Stepwatch Activity Monitor (SAM) will be mounted on the prosthetic ankle to record number of steps taken per time interval to indicate the amount of prosthetic use (Modus Health, Washington, DC). The SAM cannot be adjusted by the participant and needs to be connected to a computer with special software for programming and data downloading. It has a 99.4% accuracy in individuals with LLA for a wide range of gait styles, from slow shuffle to a fast run [64,65]. The SAM will be used to collect data in 1-week intervals at all evaluation times.

Health Utility Index Mark 3 (HUI3) is useful in performing cost-utility and cost-effectiveness analyses of new rehabilitation interventions. The HUI3 is a brief questionnaire about health status reflected in a measure of HRQOL [66]. Each single-attribute utility is scored between 0.00 and 1.00 and the multiple-attribute utility scale is scored from −0.36 to 1.00, with higher scores reflecting better health and quality of life. Test-retest reliability (ICC=.72) has been shown in patients recovering from hip fracture [67]. Differences of 0.03 have been found to represent meaningful change [68]. This study is not sufficiently powered to undertake a cost-utility analysis, but it will provide useful utility data to estimate what changes in HRQOL might be anticipated [68].

The Walking While Talking Test (WWT) is a test of divided attention to examine cognitive-motor interactions [69-72]. The WWT requires the ability to divide and switch attention between two tasks, and it has been reported that older adults show an innate preference for preserving gait over talking [73,74]. Participants walk 6 meters on a flat course, turn around, and walk 6 meters back to the start while reciting the letters of the alphabet (a, b, c, ...) aloud (WWT-simple). They repeat this routine while reciting alternate letters of the alphabet (a, c, e, …) aloud (WWT-complex). The difference in time (to the nearest second) to complete the simple and complex walks will be calculated with higher differences suggesting poorer ability to cope with dual tasks (eg, greater need to focus on walking). Inter-rater reliability (*r*=.602) and validity have been reported in older individuals [75]. The WWT will be collected with the goal of “misdirecting” participants and masking the study objectives.

The Fall Calendar will be used to document the number of falls, circumstances (eg, cause, location, assistive device used or not), and consequences participant have had (eg, medical visit, injury) over the course of study.

Adherence will be measured by total amount of the program use (minutes, frequency, and duration), which will be collected from the Wii console at the time of equipment pick-up.

### Primary Analysis

To account for any within-cluster correlation that may occur as a result of delivering the intervention in groups, ICC will be calculated among the outcomes of participants within the same groups (clusters). Variation inflation factor (VIF) will be calculated using the formula: VIF=1+ICC(M−1) [76-78]. The M variable refers to the cluster size, which equals 3 in this study. Post-treatment walking capacity scores will be compared in the Wii.n.Walk and control groups using analysis of covariance (ANCOVA) for the end of supervised phase, end of unsupervised phase, and end of retention period, controlling for site, baseline score, and possibly amputation level and age [79]. To adjust for clustering effect, the ANCOVA’s *F* statistics will be divided by the VIF [76,77]. Missing data will be handled using Multiple Imputation [80]. A sensitivity analysis will also be conducted to evaluate the impact of missing data [81]. Significance testing (*P*) and marginal means with 95% confidence intervals will be estimated. Effect size (partial eta squared) will be calculated as a ratio of the effect and total sums of squares, with a 95% confidence interval. Primary analysis will be based on intention-to-treat to include all randomized participants. However, secondary analysis on a per-protocol basis (participants who adhere to treatment) will also be conducted for comparison [82].

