### Secondary/ Tertiary Analyses

ANCOVA with an adjusted *F* statistic (as explained above) will be used to compare post-treatment scores between groups for secondary and tertiary outcomes. Confidence intervals (95%) will be derived. Mean percent adherence will be calculated.

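### The triplet-clustering correction is stated for the F statistic only, and the ICC behind it is not stated to be conditional on arm, site and baseline, so the P value and 95% CI for one contrast can disagree

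*Protocol article*

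**What the plan says.** The Primary Analysis section sets out the clustering correction as a sequence:

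- The within-triplet correlation: "ICC will be calculated among the outcomes of participants within the same groups (clusters").
- The inflation factor: "Variation inflation factor (VIF) will be calculated using the formula: VIF=1+ICC(M−1"), where "The M variable refers to the cluster size, which equals 3 in this study".
- The comparison is an ANCOVA at each of three follow-up times, "controlling for site, baseline score, and possibly amputation level and age".
- For clustering, the ANCOVA F "statistics will be divided by the VIF".
- For reporting, P values are given and "marginal means with 95% confidence intervals will be estimated".

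The Secondary/Tertiary Analyses section carries the method over as "ANCOVA with an adjusted" F statistic and adds: "Confidence intervals (95%) will be derived".

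F is the only quantity for which a clustering correction is named. The text does not say whether the ICC is computed before or after allowing for arm, site and baseline.

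**The concern.** Two features of this recipe do not fit together.

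First, dividing F by the VIF is the same as multiplying the standard error of the treatment difference by √VIF. If the interval is not widened by the same factor, one contrast is reported with two variances. The CI is then too narrow whenever triplet members resemble each other, and it can exclude zero while the adjusted P exceeds .05.

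Second, the ANCOVA F uses the residual variance after arm, site and baseline, so the ICC that belongs with it is the ICC of those residuals. An ICC of the outcomes without that conditioning is a different quantity. Baseline variance dilutes it. Because every triplet lies within one arm and one site, arm and site differences inflate it.

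At stake are the calibration of the primary P value, the coverage of the reported intervals, and a clear reading of borderline results. The same applies to every secondary and tertiary outcome analysed this way.

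**Working it through.** **Inputs from the article.** Difference 14 m, α = .05, power .90, ρ = .72, M = 3, and 72 participants in two arms at two sites, which makes 24 triplets (12 per arm). The SD used is not named. Of the four listed, only 19.9 reproduces the stated 21 per group:

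n = 2 × [19.9 × (1.960 + 1.282)/14]² × (1 − .72²) = 20.45, rounded up to 21 (two-sided α).

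**Assumed.** No ICC is given, so residual ICCs of 0 to .30 are a range chosen for this check.

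**1. P against CI.** With arm, site and baseline fitted to 72 people, the 5% critical value of F on 1 and 68 df is 3.98.

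- At ICC .10, VIF = 1 + 2 × .10 = 1.2, and the adjusted test needs F > 3.98 × 1.2 = 4.78. Any F between 3.98 and 4.78 gives an unwidened CI for the difference that excludes 0 with adjusted P > .05.
- At ICC .20, VIF = 1.4 and the zone runs to 5.57. An unadjusted P of .03 becomes .065.
- The CI half-width should be multiplied by √VIF: 1.05, 1.10, 1.18 and 1.26 at ICC .05, .10, .20 and .30. Without this, coverage is 2Φ(1.96/√VIF) − 1 = 93.8%, 92.6%, 90.2% and 87.9%.

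**2. Which ICC.** Take SD 19.9 and clustering that arises after baseline.

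- Dilution: under no effect, the unconditioned ICC is about residual ICC × (1 − ρ²). For .20 this is .20 × .4816 = .096.
- Inflation by arm: with no clustering and a true 14 m effect, the induced ICC is 7²/(7² + 19.9²) = 49/(49 + 396) = .110. VIF is then 1.22 and F falls by about 18%.

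**3. Simulation.** 24 triplets, no dropout, ρ = .72, SD 19.9, ANCOVA on arm, site and baseline, ICC estimates floored at 0, 6,000 trials per setting (Monte Carlo error about 0.3 points near 5%). All columns are percentages. Type I error and coverage are under no effect.

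| Residual ICC | Type I: no correction | Type I: F/VIF, unconditioned ICC | Type I: F/VIF, residual ICC | Type I: residual ICC, 21 df | Coverage of unwidened CI | CI excludes 0 but P > .05, at 7 m |
|---|---|---|---|---|---|---|
| 0 | 4.8 | 3.8 | 3.9 | 3.2 | 95.3 | 4.5 |
| .05 | 6.7 | 5.1 | 4.8 | 4.0 | 93.3 | 5.4 |
| .10 | 7.7 | 5.9 | 5.5 | 4.6 | 92.3 | 5.7 |
| .20 | 10.7 | 7.7 | 6.2 | 5.3 | 89.3 | 8.0 |
| .30 | 12.1 | 8.0 | 5.9 | 5.1 | 87.9 | 9.4 |

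The last column uses the unconditioned ICC. The 21 df are 24 triplets less intercept, arm and site. Disagreement occurs even at zero clustering because the estimated ICC is sometimes positive by chance.

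**4. Direction.** With an assumed 15 m site difference and residual ICC .10, the unconditioned ICC averages .171 and type I error falls to 3.9%. The error therefore has no fixed sign.

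**5. Floor.** With no clustering, the ICC estimate is negative with probability P(F(23,48) < 1) = .517. Dividing by a VIF below 1 raises F. The effect is small: type I error is about 6.0–6.1% without a floor, against 5.3–5.8% with no correction in the same runs.

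**The case against.** The authors recognised the clustering and chose a simple, cited correction. This is a condensed article, and how an ICC is estimated, whether it is floored, which df apply and how standard errors are formed are commonly left to an analysis plan. A reader might infer that the article commits to an ICC of raw outcomes and to uncorrected intervals. It states neither. The word used is outcomes, with no mention of conditioning either way, and on the intervals the text is silent. That objection stands and limits the point to what follows from the literal text.

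A reader might also infer that the P values are simply wrong, or that an effective treatment is materially penalised. The calculations do not support this. F/VIF removes much of the inflation and is near nominal at a residual ICC of .10 or less (5.4–5.9% with the floor in separate runs). The 7–8% figure needs both an unconditioned ICC and a residual ICC of about .20. The arm-induced cut in F costs under one point of power at 14 m with no clustering (98.8% to 98.1%).

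What survives is that the article does not leave the method open. It names a correction for F, names none for the intervals beside it, and extends this to all other outcomes.

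**Conclusion.** The point holds in a limited form. As written, the clustering correction reaches F but not the 95% CIs, and the ICC is not tied to the ANCOVA residual. Applied literally, P and CI disagree in about 4–8% of trials at a 7 m effect (residual ICC 0 to .20). CI coverage is about 93% at a residual ICC of .10 and 90% at .20. The P value can be miscalibrated in either direction: 7–8% type I error at .20 with an unconditioned ICC, but below 5% if site differences inflate that ICC. At a residual ICC of .10 or less, and for power at 14 m, the practical effect on the test is small.

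These sizes rest on assumed ICCs, SD 19.9, complete triplets and clustering that arises after baseline. The inconsistency between P and CI does not depend on any particular ICC: it arises whenever the estimated VIF differs from 1. It should be put right before data are seen, and the article reports no participants enrolled.

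**What to change.** Preferred: replace the F/VIF step with one linear mixed model. Arm, site and baseline score (plus any pre-set covariates) are fixed, and the training triplet has a random intercept with variance constrained to be at least 0. Use Kenward-Roger or Satterthwaite degrees of freedom. Take P, the adjusted difference, the marginal means and their 95% CIs from this model, fitted within each imputed data set, and report the residual ICC from it.

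Alternative that keeps the planned method: compute the ICC on the ANCOVA residuals, floor it at 0, multiply the standard errors and CI widths by √VIF as well as dividing F by VIF, and use triplet-based df. In the check at residual ICC .20 this gave about 5% type I error and 95% coverage.

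Use the same method for the continuous secondary and tertiary outcomes.

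The cost is analysis wording and some conservatism if there is no true clustering. Type I error is then about 3–4%. With the residual ICC and 21 df as a stand-in for the mixed model, power in the 6,000-trial runs was 98.2% at 14 m, against 98.6% for the planned F/VIF and 99.0% uncorrected. At 7 m it was 48.4%, against 51.3% and 55.7%.

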In a Single Subject Research Design (SSRD) study of six individuals with LLA, the feasibility of a Wii Fit oriented intervention consisting of structured daily training varying from 2 to 6 weeks was assessed. Results indicated a statistical improvement in walking capacity in five participants who had 3 or more weeks of intervention [30]. The aim of the present study is to extend findings on this topic and conduct a randomized controlled trial (RCT) to assess our in-home telehealth Wii Fit intervention protocol we call “Wii.n.Walk” *(*Clinicaltrial.gov NCT01942798).

The primary clinical hypothesis is that participants in the Wii.n.Walk intervention group will experience an improvement in walking capacity compared to the control group. The secondary clinical hypothesis is that participants in the Wii.n.Walk intervention group will experience an improvement in lower limb functioning (balance, gait speed, and strength), dynamic balance, physical activity, and balance confidence. The tertiary clinical hypothesis suggests that the Wii.n.Walk group will experience an improvement in life space mobility, prosthetic use, HRQOL, and will have a lower incidence of falls. The adherence hypothesis is that the Wii.n.Walk group will have ≥80% adherence.

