### Outcome Evaluation

#### Overview

Outcomes will be evaluated (Figure 1) by blinded evaluators at baseline, end of the supervised phase (week 5), end of the unsupervised phase (week 10), and end of retention period (week 62). The evaluators will be senior university students in health sciences and will have at least 1 year of experience working with research participants. They will be trained by co-investigator, BI, who has more than 5 years of experience working with amputees and administering the outcome measures used in this study.

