#### Primary Outcome Measure

The Two-Minute Walk Test (2MWT) will be used to measure walking capacity as the primary outcome measure. Starting from a standing position, participants will be asked to walk as far as they can in a safe manner for 2 minutes over an indoor, flat, out-and-back course. The distance travelled to the nearest meter is recorded. The Canadian Physical Medicine and Rehabilitation Association’s Amputee Special Interest Group [40], and others [41,42], have recommended the 2MWT as the preferred measure of walking capacity. It is used in more trials of individuals with LLA [43-53] than any other measure, enabling us to compare our results with previous studies. The 2MWT has been validated with a number of LLA samples [41,42,51-53]. The 2MWT has demonstrated intra-rater reliability (intraclass correlation coefficient/ICC=.96), inter-rater reliability (ICC=.98) [51], and validity and responsiveness to change (mean 13.6, SD 19.9 meters) in individuals with LLA [52].

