### Sample Size Calculation

The primary outcome (2MWT) was used to calculate the sample size. The responsiveness of the 2MWT in a single study that included older adults with LLA being discharged from rehabilitation had a mean of 13.6 (SD 19.9) meters [52]. In an RCT of younger (mean age 36 years) community-dwelling individuals with LLA, the mean difference between treatment and control groups was 11.2 (SD 18.4) meters [43]. Walking distance gains from our own pilot work (mean 25, SD 18.1 meters) on younger adults in rehabilitation [30], and early results from our feasibility study (mean 11.9, SD 9.3 meters) using a similar sample as the proposed study, suggests distances of up to 14 meter gains may be possible. Taking into account these data and based on our study team’s considerable clinical expertise, we decided that the minimal clinically important difference of 14 meters would be reasonable. Using the sample size calculation formula for ANCOVA in RCTs (α=.05; β=.1; rho=.72) [82], each group would require 21 participants. Borm et al [83] demonstrate that when rho lies between .2 and .8, ANCOVA further reduces the required sample size by 10-40% over change score. Accounting for an additional 4 degrees of freedom (one stratification factor for site at randomization and possibly three at analysis), an extra four participants per group (n=25) are required. Accounting for a conservative total group dropout rate of 25% and supported by physical activity clinical trials (8-24%) [84,85], 64 participants are required. Because the supervised sessions are conducted in groups of three, the sample size needs to be divisible by three. Therefore, a final n=72 will allow us to enroll a balanced n of 18 Wii.n.Walk and 18 controls at each site.

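### The primary analysis compares the 2MWT at three visits on equal footing, with no primary time point, ordering or multiplicity rule, while the sample size covers a single comparison

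*Protocol article*

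**What the plan says.** The Introduction states one primary hypothesis, that "participants in the Wii.n.Walk intervention group will experience an improvement in walking capacity compared to the control group", and attaches no time point to it. The Primary Outcome Measure section says "The Two-Minute Walk Test (2MWT) will be used to measure walking capacity as the primary outcome measure", again without a visit. The Outcome Evaluation overview schedules post-baseline assessments at "end of the supervised phase (week 5), end of the unsupervised phase (week 10), and end of retention period (week 62".

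The Primary Analysis section then applies ANCOVA "for the end of supervised phase, end of unsupervised phase, and end of retention period, controlling for site, baseline score". It asks for P values and says that "marginal means with 95% confidence intervals will be estimated". It divides the F statistic by a variance inflation factor to allow for clustering in the training groups. It describes no ranking of the visits, no joint test and no adjustment for multiple testing.

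The Sample Size Calculation section uses one set of design values, "α=.05; β=.1; rho=.72", and one difference: "we decided that the minimal clinically important difference of 14 meters would be reasonable". It does not say at which visit that difference is expected. It arrives at 21 per group, adds four for covariates, and ends at 72 in total (36 per group) after allowing for dropout and groups of three.

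**The concern.** One hypothesis is matched to three between-group tests that carry equal weight, and the protocol does not say which of them decides it. If a favourable result at any visit can be presented as confirming the hypothesis, the error rate of the trial's main claim exceeds the 5% on which the trial was sized.

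The three visits also measure different things: the effect after supervised training, the effect after a further four weeks of optional use, and retention about a year later. A mixed pattern, such as a difference at week 5 and none at week 62, is quite possible. The plan gives no rule for reading it, which leaves room to choose the visit to emphasise once results are known.

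**Working it through.** **Step 1. Reproduce the stated 21 per group.** Inputs from the Sample Size Calculation section: difference 14 m, α=.05, power 90%, rho=.72. The design SD is not named, so each SD quoted there was tried. The formula is

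n = 2 × (z₁₋α/₂ + z₁₋β)² × SD² × (1 − rho²) / difference²

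With a two-sided test and SD 19.9: 2 × (1.960 + 1.282)² × 19.9² / 14² = 42.46, and 42.46 × (1 − .72²) = 42.46 × .4816 = 20.45, rounded up to 21. The stated figure reproduces. The other two-sided candidates do not: SD 18.4 gives 18, SD 18.1 gives 17 and SD 9.3 gives 5. SD 19.9 with a one-sided test gives 17. So the trial was sized for one two-sided comparison at .05.

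**Step 2. Correlation between the three tests.** The article gives only rho=.72, between baseline and follow-up. If every pair of visits is assumed to correlate at .72, two follow-up scores adjusted for baseline correlate at

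(.72 − .72²) / (1 − .72²) = .2016 / .4816 = .42

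If follow-up visits instead correlate at .9 with each other, the adjusted value is (.9 − .5184) / .4816 = .79.

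**Step 3. Chance of at least one false positive in three tests.** Assumptions: no true effect at any visit, each test two-sided at .05, clustering correctly handled, and any one significant visit counts. With independent tests the two-sided rate is 1 − .95³ = 14.3%, and the rate favouring Wii.n.Walk is 1 − .975³ = 7.3%. For correlated tests, three equally correlated normal statistics were simulated (3 million draws, cut-off 1.96):

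| Correlation of the tests | Either direction | Favouring Wii.n.Walk |
|---|---|---|
| 0 | 14.3% | 7.3% |
| .42 (implied by .72 throughout) | 13.0% | 6.5% |
| .60 | 11.8% | 5.9% |
| .72 | 10.7% | 5.4% |
| .80 | 9.8% | 4.9% |
| .90 | 8.4% | 4.2% |
| One test, for reference | 5.0% | 2.5% |

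**Step 4. What the remedies cost in N.** One designated time point keeps α=.05 for that test, so 21 per group is unchanged. A Bonferroni split (.05/3 = .0167) needs 27 per group. With the plan's four extra that is 31, and 31/.75 = 41.3, so 42 per group against 36 planned. If 25% of the 36 are lost, 36 × .75 = 27 remain. By the normal approximation, without the covariate allowance, power is then about 96% for one test at .05 and about 91% at .0167.

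**The case against.** Several points on the other side are fair and limit what can be claimed.

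- **Per-test alpha.** A reader might infer that the protocol fixes α=.05 for each visit. It does not say so. Alpha appears once, in the sample size. A per-test .05 is inferred from that single value, the 95% confidence intervals and the absence of any adjustment.
- **Any one success counts.** This rule is not written either. The visits follow distinct phases and can be read as three questions reported separately. If all three had to be significant, type I error would be controlled, but the sample size calculation would not give the power for that criterion. The text does not say which reading applies.
- **A flat 13% in place of 5%.** This is the tempting headline, and the document does not support it. It needs a correlation of .72 between every pair of visits, although weeks 5 and 10 are close together and week 62 is a year later. It also counts false findings in either direction, whereas the hypothesis is one of improvement.
- **Power.** It would be wrong to infer that the trial is underpowered or that the 90% is meaningless. The calculation holds for any single visit under the same inputs, and 36 per group leaves some slack.
- **A separate analysis plan.** A statistical analysis plan may contain a multiplicity rule, and its absence from an article would not by itself be a finding. What remains is what the article does state: three tests under the primary heading, none ranked, beside a sample size for one. The time point belongs to the definition of the primary outcome.

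**Conclusion.** The point holds in conditional form. The protocol places three comparisons of the 2MWT in its primary analysis without a primary time point, ordering or adjustment, and its sample size is a single two-sided comparison at .05.

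If each test uses .05 and any one visit may be taken as support, the chance of at least one false positive lies between 8.4% and 14.3% two-sided, for correlations between the tests from .9 down to 0. In favour of Wii.n.Walk the range is 4.2% to 7.3% against 2.5%. The exact size depends on a correlation that the article does not give. The direction does not: the rate exceeds nominal at every value examined. Dividing F by the variance inflation factor deals with clustering and does not change this.

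**What to change.** Before enrolment, name one primary time point in the hypothesis, the outcome definition and the primary analysis. The end of the supervised phase (week 5) is one example, and the choice is the investigators'. State that the 14 m difference, the sample size and the 90% power refer to that visit. Then either label the other two visits secondary, or test them in a fixed sequence (for example week 5, then 10, then 62), each at α=.05 and only if the preceding test is significant.

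This takes a few sentences and leaves N at 72, with power for the first test unchanged. The article reports that nobody had yet been enrolled, so the change could be made without reference to any data. The cost is that a later visit cannot be claimed as confirmatory if the first test fails. If all three visits are to stand as equal primaries, a Bonferroni split is an alternative, but under the plan's own allowances it would call for 42 per group rather than 36.

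### The primary analysis names partial eta squared as its effect size but not the adjusted between-arm 2MWT difference in metres with a clustering-corrected interval, although the trial is sized on a 14 m difference

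*Protocol article*

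**What the plan says.** Primary Analysis compares post-treatment two-minute walk distance between arms by ANCOVA, controlling for site and baseline and possibly for amputation level and age. It then lists the outputs. Besides a P value, "marginal means with 95% confidence intervals will be estimated. Effect size (partial eta squared) will be calculated as a ratio" of effect to total sums of squares, itself with a 95% interval.

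Clustering within training triplets is handled by VIF = 1 + ICC(M − 1): "The M variable refers to the cluster size, which equals 3 in this study". The only quantity the section divides by the VIF is the F statistic. No ICC value is given.

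The outcome is in metres: "The distance travelled to the nearest meter is recorded" (Primary Outcome Measure). So is the planning target: "we decided that the minimal clinically important difference of 14 meters would be reasonable" (Sample Size Calculation).

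Secondary/ Tertiary Analyses repeats the ANCOVA with the adjusted F and promises 95% intervals, without saying for which quantity.

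**The concern.** The design asks its question in metres between arms. The quantity that answers it, the adjusted mean difference with its interval, is not among the named outputs. This is more than silence that an analysis plan might fill, because the article positively chooses a unit-free proportion of variance as the effect size.

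There are three consequences:

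- A mean and interval for each arm is not an interval for the difference between arms.
- Eta squared depends on how varied the sample is, so it cannot be set against 14 m or against the between-group difference of 11.2 m that Sample Size Calculation cites from another trial.
- With the VIF applied to F alone, the P value allows for clustering and the reported intervals do not.

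The stake is how the primary result is read. A significant result could be published with an effect size while the reader is not shown how far below or above 14 m the true difference may lie. A non-significant result would not show directly whether 14 m remains plausible.

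**Working it through.** **Inputs.** From Sample Size Calculation: target 14 m, α = .05, power .90, rho = .72, dropout 25%, N = 72, and candidate SDs of 19.9, 18.4 and 9.3 m. From Primary Analysis: M = 3. Assumptions: the SD used for planning was 19.9 (not stated; inferred in step 1); 27 completers per arm (72 × 0.75 ÷ 2); ICC from 0 to 0.10; residual df = 2n − 5 = 49.

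**1. The plan's own figure.** Adjusted SD = 19.9 × √(1 − .72²) = 13.81 m. Then n per group = 2 × [13.81 × (1.960 + 1.282) / 14]² = 20.45, rounded up to 21 as stated. The same two-sided formula gives 18 with SD 18.4, and a one-sided test with SD 19.9 gives 17. So 19.9, two-sided, is the reading that fits, and 14 m is the planning quantity.

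**2. Precision of the difference, no clustering.** SE = 13.81 × √(2/27) = 3.76 m. With t(.975, 49) = 2.01, the 95% half-width is 7.6 m (7.55 before rounding). Each arm's own interval has half-width 2.01 × 13.81 / √27 = 5.3 m, so neither arm interval shows the uncertainty of the comparison.

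**3. A significant 8 m.** t = 8 / 3.76 = 2.13, so the result is significant. Its interval is 8 ± 7.55, about 0.4 to 15.6 m. Partial eta squared = t² / (t² + 49) = 4.53 / 53.53 = .085.

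**4. With clustering.** Dividing F by the VIF is equivalent to multiplying the SE by √VIF.

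| Assumed ICC | VIF | 95% half-width | Interval around 8 m |
|---|---|---|---|
| 0 | 1.00 | 7.6 m | 0.4 to 15.6 m |
| 0.05 | 1.10 | 7.9 m | 0.1 to 15.9 m |
| 0.10 | 1.20 | 8.3 m | −0.3 to 16.3 m |

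At ICC 0.10 the corrected test on 8 m is no longer significant, while an uncorrected interval for the difference would still exclude zero.

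**5. Other planning values.** With SD 18.4 and 27 per arm the half-width is 7.0 m (7.3 to 7.7 m at ICC 0.05 to 0.10). With SD 19.9 and all 36 per arm it is 6.5 m (6.8 to 7.1 m).

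**6. Eta squared for a fixed 14 m.** This takes 27 per arm and rho .72, and treats each quoted SD as the outcome SD.

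- SD 19.9: F = (14 / 3.76)² = 13.87; 13.87 / (13.87 + 49) = 0.22.
- SD 18.4: F = 16.23; 16.23 / 65.23 = 0.25.
- SD 9.3: adjusted SD 6.45, SE 1.76, F = 63.5; 63.5 / 112.5 = 0.56.

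One difference in metres thus maps to values from 0.22 to 0.56 across SDs that the article itself quotes.

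**The case against.** The strongest reply is that nothing is lost. ANCOVA marginal means are adjusted and in metres, so subtracting them gives the adjusted difference. With two arms, SE = |difference| / √F, or |difference| / √(F/VIF) after the planned correction, and F can be recovered from an exact P and its degrees of freedom. A reader might infer from this concern that the result cannot be judged against 14 m at all. The article does not support that: the point estimate is available by subtraction, and an interval can be reconstructed if F or an exact P is published. What remains is that the primary estimate's interval should not have to be reconstructed by readers, least of all when the printed intervals omit a correction that the P value includes.

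Second, this is a condensed article, and an analysis plan not shown may list the contrast. That is fair for anything merely unmentioned. It does not cover the stated choice of eta squared as the effect size, or the stated restriction of the VIF to F.

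Third, the wording does not explicitly confine the intervals to single arms. It is loose, but an interval for a marginal mean is ordinarily an interval for one arm.

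Fourth, a reader might take significance at about half of 14 m as a fault, or say that a significant result would exclude nothing below 14 m. Neither stands. Any trial with 90% power reaches significance well below its target (1.96 / 3.24, about 60%, and lower here because N was raised), and 0.4 to 15.6 m does exclude values below 0.4 m. Nor does the plan invite anyone to judge significance by whether arm intervals overlap.

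Finally, 14 m is used to size the trial and is not a decision margin, so a formal rule at 14 m would be a preference and not a correction.

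**Conclusion.** The concern holds as a reporting point that should be fixed. The named outputs centre on an effect measure that varies with sample spread. They do not directly give an interval for the between-arm difference on which the trial is sized, and the intervals they do give would lack the clustering correction used for the P value. The uncertainty left out of direct view is about ±7.6 m without clustering and ±7.9 to 8.3 m at an ICC of 0.05 to 0.10, which is more than half of the 14 m target.

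These figures rest on SD 19.9 (inferred because it reproduces 21 per group), rho .72, 27 completers per arm and assumed ICCs. With the other values tried, the half-width stays between 6.5 and 7.7 m.

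The point does not show that the test is invalid, that the sample size is wrong, or that the result could not be compared with 14 m.

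**What to change.** In Primary Analysis, name as the primary estimate the adjusted mean 2MWT difference (Wii.n.Walk minus control), in metres, with a 95% interval at each assessment. Obtain the interval in one of two ways, so that it agrees with the P value:

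- multiply the ANCOVA standard error of the difference by √VIF, which matches dividing F by the VIF; or
- take both the interval and the P value from one model that accounts for the triplets.

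Discuss the estimate and its limits against 0 and 14 m, without a formal decision rule. Keep the marginal means as description and make eta squared optional. In Secondary/ Tertiary Analyses, say that the promised intervals are for the adjusted between-arm difference in each measure's natural units, with the same correction.

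The cost is wording and a little extra analysis work, since plain ANCOVA output does not itself contain the corrected interval. The intervals will be slightly wider than uncorrected ones, by a factor of √1.10 = 1.05 to √1.20 = 1.10 at an ICC of 0.05 to 0.10. N is unchanged. The article's Results section reports no enrolment yet, so at that stage the change could be made before any data existed.
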